### Sample size calculation

The sample size for this prospective study was determined according to binomial receiver operating characteristic curve analysis performed in diagnostic accuracy studies by a biostatistician ([name], with 12 years of experience). The sample size was calculated using PASS 15 Power Analysis and Sample Size (NCSS, Kaysville, Utah, ncss.com/software/pass). The null hypothesis of an area under the curve (AUC) of 0.7 was compared with an alternative hypothesis of an AUC of 0.85 for the tumor habitat analysis for the determination of RN. The target distribution was the rate of RN versus tumor recurrence, which is known to be detected in a 1:2 ratio in post-treatment BM [4]. With an alpha of 0.05 (type-1 error) and a beta of 0.20 (type-2 error), 34 positive cases (RN) and 68 negative cases (tumor recurrence), giving a total of 102 cases, were identified as the appropriate sample size. Considering a dropout rate of 10% and a censoring rate of 20% for BM, 132 patients were found to be appropriate for the study design.

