## Background

Stereotactic radiosurgery (SRS) has emerged as the standard of care for patients who have relatively few brain metastases (BMs) and do not require immediate relief of mass-related symptoms [1, 2]. However, challenges arise when an enlarging enhancing lesion is observed during follow-up magnetic resonance imaging (MRI) after SRS, as this lesion may indicate either tumor progression or radiation necrosis (RN). The incidence of RN following SRS is reported to range from 5 to 26% per treated lesion [3, 4]. Differentiating RN from tumor progression is crucial for patient management because the treatment strategies for these two conditions are substantially different. For recurrent tumors, repeat SRS or surgical resection may be considered, whereas additional radiotherapy should be avoided in cases of RN [5, 6].

On perfusion MRI, the relative cerebral blood volume (CBV) and cerebral blood flow (CBF) have shown pooled sensitivity and specificity values of around 85% and 81%, respectively, in distinguishing tumor progression from RN [7]. Nonetheless, the frequent coexistence of tumor recurrence and radiation injury in post-treatment tumors [8] and the heterogeneous nature of such tumors present significant challenges to the evaluation of post-treatment lesions using single quantitative parameters. A single parameter is only capable of providing information in one direction or a linear correlation, which limits the comprehensive characterization of post-treatment tumors. In this respect, pattern analysis combining quantitative parameters [9] may improve discrimination ability and tissue characterization in metastatic tumors after high-dose SRS.

Tumor habitat analysis aims to identify distinct subregions within a complex tumor by clustering similar voxels that share common tumor biology [10, 11]. A recent retrospective longitudinal study with diffusion-weighted and dynamic susceptibility contrast (DSC) imaging showed the feasibility of tumor habitat analysis, which reflects information on tumor cellularity and tumor vascularity [12]. This study demonstrated that an increase in hypovascular cellular habitat (low CBV and low apparent diffusion coefficient [ADC]) is predictive of early recurrence of BM after SRS.

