## Methods

### Study objectives

#### Primary objective

This study aims to evaluate a multi-parametric MRI-based tumor habitat imaging biomarker for determining tumor recurrence after SRS for BMs. The primary outcome measure is the time to recurrence, calculated from the date of SRS for BMs until the date of progression assessed according to the Response Assessment in Neuro-Oncology Brain Metastases (RANO-BM) criteria. The timeframe will be restricted to up to 24 months after SRS.

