### Statistical analysis

Analysis of the association between the tumor habitats and time to recurrence will be conducted using Cox proportional hazards regression analysis. The imaging predictor exhibiting a strong association will be selected on the basis of both univariate and multivariable Cox proportional regression analysis. Adjustments for time-dependent covariates will be made.

The prediction model for time to recurrence will be created by combining imaging predictors and clinical variables. The performance of the prediction model will be analyzed using C-statistics and time-dependent receiver operating characteristic curve analysis, and calibration (Hosmer-Lemeshow goodness-of-fit test) will be evaluated.

The Dice similarity coefficient will be calculated when the recurrence is diagnosed. The area of each habitat before SRS will be divided by the contrast-enhancing lesion at the time of tumor recurrence.

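### The 80% power belongs to a radiation-necrosis AUC test outside the primary outcome and the described analyses, and the step from 102 cases to 132 patients does not secure it

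*Protocol article*

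**What the plan says.** - **Primary objective:** "The primary outcome measure is the time to recurrence", defined by RANO-BM progression and limited to 24 months after radiosurgery (SRS). The secondary objectives mention RN only through its occurrence rate.
- **Sample size calculation:** "The null hypothesis of an area under the curve (AUC) of 0.7 was compared with an alternative hypothesis of an AUC of 0.85". The quantity tested is how well habitat analysis identifies RN as opposed to recurrence. Alpha is 0.05 and beta 0.20. RN and recurrence are said to be "known to be detected in a 1:2 ratio in post-treatment BM". The result is "34 positive cases (RN) and 68 negative cases (tumor recurrence), giving a total of 102 cases, were identified as the appropriate sample size". Allowing for 10% dropout and 20% censoring, the section arrives at 132 patients.
- **Statistical analysis:** "Analysis of the association between the tumor habitats and time to recurrence will be conducted using Cox proportional hazards regression analysis". A prediction model for time to recurrence follows, assessed by C-statistics, time-dependent ROC curves and calibration, and then Dice coefficients.
- **Background:** "The incidence of RN following SRS is reported to range from 5 to 26% per treated lesion".
- **Inclusion criteria:** one to ten new metastases, with a longest diameter above 1.5 cm for habitat analysis.

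**The concern.** Two things do not fit together.

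First, the only power statement in the article belongs to a test that discriminates RN from recurrence. That test is not the primary outcome, is not among the secondary objectives, and is not one of the analyses described. The ROC analysis that is described evaluates the time-to-recurrence model, so it is a different analysis. The primary Cox analysis therefore has no stated basis for its size.

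Second, the calculation counts cases already known to be RN or recurrence, whereas the cohort is recruited before SRS. The inflation from 102 to 132 allows for dropout and censoring only. It makes no allowance for patients who respond or stay stable, although the Reference standard section defines complete response, partial response and stable disease.

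At stake is whether 80% power can be quoted for this study at all, and whether a reader can tell what the primary analysis is able to detect.

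**Working it through.** **1. Reproduce the case count.** Inputs from the Sample size calculation: AUC 0.70 vs 0.85, alpha 0.05, power 0.80, ratio 1:2. Sidedness is not stated; two-sided is the choice that reproduces the figure.

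Hanley-McNeil variance, with a RN and b recurrence cases:

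V(A) = [A(1-A) + (a-1)(q1-A²) + (b-1)(q2-A²)] / (ab), with q1 = A/(2-A) and q2 = 2A²/(1+A).

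Power = Φ{[0.15 - 1.96·√V(0.70)] / √V(0.85)}.

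At a = 34, b = 68: √V(0.70) = 0.0573 and √V(0.85) = 0.0446, so power = Φ[(0.15 - 0.1124)/0.0446] = 80.0%. The count of 102 is correct for the test it names. A binormal variance gives about 36 + 72, which is a small difference.

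**2. The step to 132.** 102 x 1.30 = 132.6, so the losses were added to the case count. Working back from 132:

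- 132 x 0.9 x 0.8 = 95 patients, or 132 x 0.7 = 92 patients. Both are below 102.
- If every one of 95 were a case, the 1:2 split is about 32 RN and 63 recurrence, power about 77%.
- Dividing by retention gives 102/0.72 = 142 or 102/0.70 = 146.

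This step needs only one case per patient and no incidence figure.

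**3. RN yield.** Assumptions: one analysed lesion per patient; RN incidence 5-26% (Background); recurrences at twice the RN count; losses unrelated to outcome. The 15.5% column is the arithmetic midpoint of the range, used for illustration only.

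| RN incidence | 5% | 15.5% | 26% |
|---|---|---|---|
| RN cases, 132 patients, no loss | 7 | 20 | 34 |
| RN cases, 95 patients (both losses) | 5 | 15 | 25 |
| Recurrences at 1:2, 95 patients | 10 | 30 | 50 |
| Power of the AUC test, 95 patients | 10% | 38% | 64% |

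The normal approximation is rough at 5 RN cases. If every other retained patient counted as a recurrence, power would be about 14%, 45% and 67%, so the number of RN cases is the main limit.

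**4. Lesions as the unit.** Lesions needed per retained patient to reach 34 RN, with 95 patients: 34/(0.26 x 95) = 1.4; 34/(0.155 x 95) = 2.3; 34/(0.05 x 95) = 7.2. The article does not give the number of analysable lesions per patient. Lesions within a patient are correlated, while the formula in step 1 assumes independent cases.

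**The case against.** The strongest objection concerns the unit. The incidence is per treated lesion, patients may have up to ten metastases, and response is assessed per lesion as well as per patient. With enough lesions above 1.5 cm, 34 RN cases could be reached. This stands. A reader might infer that 132 patients cannot supply 34 RN at the protocol's own incidence; the documents do not support that. The shortfall in step 3 is conditional on one analysed lesion per patient, and even then the target is just met at 26% with no loss (132 x 0.26 = 34.3).

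A reader might also want to turn the yields into a detectable hazard ratio for the Cox analysis by treating adjudicated recurrences as events. That is not supported either. The Progressive disease definition counts a lesion that meets the growth rule as progression even when signs of RN are mixed in, so primary events are not the same as adjudicated recurrences. The article gives no recurrence rate from which to count them.

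Finally, this is a condensed article, and the full protocol or analysis plan may describe a secondary RN AUC. That is fair, and silence alone would be no finding. What remains is a mismatch between stated items: the article sizes the study on one quantity, declares another primary and describes the analysis of that other one. An RN AUC reported with a confidence interval would also remain interpretable at a low yield; it is the 80% power claim that fails.

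**Conclusion.** The point holds in a limited form.

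- **Without further assumption:** the stated 80% power is for an RN-versus-recurrence test that is neither the primary outcome nor among the described analyses.
- **With one case per patient:** the protocol's own losses leave 92 to 95 patients against 102 required cases, so power is about 77% at best on its own formula.
- **With one analysed lesion per patient, 5-26% RN and the 1:2 ratio:** about 5 to 25 RN cases and power of about 10-64%.
- **With several lesions per patient:** 34 RN may be reachable, but the independent-case formula no longer applies.

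The arithmetic giving 34 + 68 is not in question. The article does not allow the power of the Cox analysis to be judged in either direction.

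**What to change.** Keep 132 patients and rewrite the Sample size calculation:

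1. State whether a case is a patient or a lesion. If a lesion, allow for clustering within patients.
2. Base the justification on the primary Cox analysis. Give the detectable hazard ratio per standard deviation of the habitat parameter over a stated range of RANO-BM progression events, marked as an assumption because the article gives no recurrence rate.
3. Drop the 80% power claim. Present the RN AUC as a secondary estimate with its expected 95% confidence half-width, 1.96·√V(0.85), over the plausible yield. At an AUC of 0.85 and with independent cases this is about ±0.10 with 25 RN and 50 recurrences, ±0.13 with 15 and 30, and ±0.24 with 5 and 10.
4. Name that AUC analysis in the Statistical analysis section, among cases adjudicated as RN or recurrence.

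The cost is one rewritten paragraph, one added sentence on the analysis, and less favourable stated figures. No extra patients are needed and clinical care does not change.

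### The enrolment target of 132 does not leave the required 102 cases after the plan's own losses: it leaves 92 to 95, with about 75–77% power instead of 80%

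*Protocol article*

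**What the plan says.** The Sample size calculation section of the protocol article bases the size on a one-sample ROC comparison for determining radiation necrosis (RN): "The null hypothesis of an area under the curve (AUC) of 0.7 was compared with an alternative hypothesis of an AUC of 0.85". The error rates are "With an alpha of 0.05 (type-1 error) and a beta of 0.20 (type-2 error"), and RN versus recurrence is taken as "known to be detected in a 1:2 ratio in post-treatment BM". The result is "34 positive cases (RN) and 68 negative cases (tumor recurrence), giving a total of 102 cases".

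The section then moves from evaluable cases to enrolled patients in one step: "Considering a dropout rate of 10% and a censoring rate of 20% for BM, 132 patients were found to be appropriate". No inflation formula is given, and the text does not say that one of the two loss rates contains the other.

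**The concern.** An allowance for loss should set enrolment so that the required number remains once the losses have happened. That means dividing the required number by the fraction retained. Multiplying it by one plus the loss rate always gives too few, and the gap widens as the loss grows. At a combined loss near 30% the gap is no longer a matter of rounding.

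The 102 cases sit exactly at the 80% power threshold, with no margin. Any shortfall in yield therefore takes power below the stated figure. This calculation is the only justification the article offers for enrolling 132, and a reader will take that number to secure 80% power after attrition.

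**Working it through.** **Inputs**, all from Sample size calculation: AUC 0.70 under the null and 0.85 under the alternative; alpha 0.05; beta 0.20; RN to recurrence 1:2; 34 + 68 = 102 cases; dropout 10%; censoring 20%; 132 patients. Whether the test is one- or two-sided is not stated.

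**1. Reproduce the 102.** I used a one-sample z-test on the AUC with the Hanley–McNeil variance:

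Var(A) = [A(1−A) + (n₁−1)(Q₁−A²) + (n₂−1)(Q₂−A²)] / (n₁n₂), with Q₁ = A/(2−A), Q₂ = 2A²/(1+A), n₁ = RN cases and n₂ = recurrence cases.

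Power = Φ[(0.15 − 1.96 × SE₀)/SE₁], where SE₀ is taken at 0.70 and SE₁ at 0.85.

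At 34 and 68, SE₀ = 0.0573 and SE₁ = 0.0446. The argument is 0.843 and power is 80.0%. The smallest 1:2 design that reaches 80% is exactly 34 and 68, so the plan's case number is reproduced. The one-sided version needs only 27 and 54, so two-sided is the reading that fits.

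**2. Look for the route from 102 to 132.**

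| Rule | Result |
|---|---|
| 102 × 1.30 | 132.6 |
| 102 × 1.1 × 1.2 | 134.6 |
| 102 / 0.90 (dropout only) | 113.3 |
| 102 / 0.80 (censoring only) | 127.5 |
| 102 / (0.90 × 0.80) | 141.7 |
| 102 / 0.70 | 145.7 |

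Only the first lands on 132, with the decimal dropped. Adding 10% and 20% of 102 as whole numbers gives the same: 102 + 10 + 20 = 132.

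**3. Apply the stated losses to 132.** This step does not depend on how 132 was obtained.

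- Losses in sequence: 132 × 0.90 × 0.80 = 95.0 cases, 7 short of 102.
- Losses added: 132 × 0.70 = 92.4 cases, about 10 short.

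Retaining 102 of 132 would require a total loss of 1 − 102/132 = 22.7%. The stated rates combine to 28% (sequential) or 30% (additive).

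**4. Power at that yield**, same method and 1:2 ratio:

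| Cases | RN / recurrence | Power |
|---|---|---|
| 102 | 34 / 68 | 80.0% |
| 95.0 | 31.7 / 63.4 | 76.6% |
| 92.4 | 30.8 / 61.6 | 75.1% |

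A binormal variance evaluated at the null also reproduces 34 and 68 (80.2%). It gives 77.4% at 95.0 cases and 76.3% at 92.4, so the drop does not hinge on the variance formula.

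**5. Enrolment that keeps 102.** 142 × 0.72 = 102.2 and 146 × 0.70 = 102.2. The target is therefore 10 to 14 patients too low.

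**The case against.** Four points can be made for the plan as it stands.

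*Censoring may already contain dropout.* In a time-to-event study, a patient who leaves before the event is normally censored. If the 20% includes the 10%, 132 × 0.80 = 105.6 and the target is sufficient. This cannot be excluded, but nothing in the text supports it: the sentence names two separate rates, and on that reading the target would be 128, not 132.

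*The multiplication is inferred.* That is true, since no formula is printed and 132.6 reaches 132 only by truncation. The mismatch in step 3 does not depend on the inference.

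*The yield of 92 to 95 is itself uncertain.* It accepts the plan's premise that each retained patient supplies one RN or recurrence case. Under the Reference standard section some patients may respond or stay stable and be neither. In the other direction, patients may have up to ten metastases and response is also assessed per lesion. This point stands: 92 to 95 is what the plan's own assumptions imply, not a forecast.

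*The primary outcome is something else.* Time to recurrence is analysed by Cox regression, and the Statistical analysis section describes no test of 0.85 against 0.70 for RN. The shortfall therefore does not bear directly on the primary analysis. That limits the consequence but does not repair the sum.

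**Conclusion.** The concern holds. The required cases, the two loss rates and the enrolment target are all printed, and they are inconsistent. Under the plan's own losses, 132 patients give 92 to 95 cases instead of 102, a shortfall of 7 to 10 cases (7–9%). RN cases number 31 to 32 instead of 34, and power is about 75–77% instead of 80%.

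This rests on three assumptions: a two-sided test, which is the reading that reproduces 34 and 68; losses that do not overlap, as the sentence lists them; and the plan's premise of one case per retained patient at 1:2. The size is modest, 3 to 5 points of power. The statement is nevertheless wrong as written and should be corrected.

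**What to change.** Amend the last sentence of Sample size calculation in one of two ways:

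- state the target as 142 (losses in sequence) or 146 (losses added), showing the division by the retained fraction; or
- keep 132 and state that, after the assumed losses, 92 to 95 cases are expected (31–32 RN, 62–63 recurrence), with power of about 75–77%.

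Either way, name the formula and say whether censoring includes dropout. If it does, saying so and showing 132 × 0.80 = 105.6 settles the matter without changing the number.

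Restating costs one sentence and a slightly less favourable power figure, with no extra patients. Raising the target costs 10 to 14 more patients.

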### Statistical analysis

Analysis of the association between the tumor habitats and time to recurrence will be conducted using Cox proportional hazards regression analysis. The imaging predictor exhibiting a strong association will be selected on the basis of both univariate and multivariable Cox proportional regression analysis. Adjustments for time-dependent covariates will be made.

The prediction model for time to recurrence will be created by combining imaging predictors and clinical variables. The performance of the prediction model will be analyzed using C-statistics and time-dependent receiver operating characteristic curve analysis, and calibration (Hosmer-Lemeshow goodness-of-fit test) will be evaluated.

The Dice similarity coefficient will be calculated when the recurrence is diagnosed. The area of each habitat before SRS will be divided by the contrast-enhancing lesion at the time of tumor recurrence.

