## Abstract

**Background:**

The identification of viable tumors and radiation necrosis after stereotactic radiosurgery (SRS) is crucial for patient management. Tumor habitat analysis involving the grouping of similar voxels can identify subregions that share common biology and enable the depiction of areas of tumor recurrence and treatment-induced change. This study aims to validate an imaging biomarker for tumor recurrence after SRS for brain metastasis by conducting tumor habitat analysis using multi-parametric MRI.

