For an imaging biomarker to be used as a generalizable tool, a prospective study is required to ensure that the biomarker provides a reliable quantitative assessment of treatment responses. Our study aims to validate an imaging risk for tumor recurrence after SRS on patients with BMs by conducting tumor habitat analysis using multi-parametric MRI.

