### Study design

This prospective single-arm observational cohort study aims to investigate the value of multi-parametric MRI for predicting recurrence in patients with BMs who are treated with SRS. Patients will undergo the standard care protocol for their metastases. This study will not incorporate any interventions.

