The imaging biomarker developed in this prospective study will provide an objective and reliable measure for assessing tumor recurrence following SRS. Identification of the subregions at increased risk of recurrence will facilitate the establishment of an optimal strategy for close monitoring of therapeutic targets and distinguishing nonviable tumor areas that can be considered safe for observation. Such an accurate imaging assessment of tumor progression or radiation-induced change will help avoid unnecessary surgery or radiation therapy, thereby minimizing associated patient morbidity.

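### The study says it will validate a habitat biomarker, but the analysis selects the predictor and builds and assesses the model in one cohort, which is development

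*Protocol article*

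**What the plan says.** The Background of the abstract states: "This study aims to validate an imaging biomarker for tumor recurrence after SRS for brain metastasis". The main Background repeats the aim: "Our study aims to validate an imaging risk for tumor recurrence after SRS on patients with BMs". It also reports an earlier retrospective study in which growth of the hypovascular cellular habitat (low CBV, low ADC) "is predictive of early recurrence of BM after SRS".

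The Statistical analysis section first relates the habitats to time to recurrence by Cox regression. It then says: "The imaging predictor exhibiting a strong association will be selected on the basis of both univariate and multivariable Cox proportional regression analysis". Next: "The prediction model for time to recurrence will be created by combining imaging predictors and clinical variables". Then: "The performance of the prediction model will be analyzed using C-statistics and time-dependent receiver operating characteristic curve analysis", together with a calibration test.

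Study design describes a single cohort: "This prospective single-arm observational cohort study aims to investigate the value of multi-parametric MRI for predicting recurrence". The Discussion calls the product something made here: "The imaging biomarker developed in this prospective study will provide an objective and reliable measure".

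**The concern.** To validate a biomarker is to fix it beforehand (which habitat, which measure, which scan, which form) and see whether it performs in patients who played no part in choosing it. Here the same patients choose the predictor, supply the model coefficients and provide the performance figures.

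Two things follow. A claim that some habitat predicts recurrence has no controlled type I error, because several candidates compete and the strong one is kept. And a C-statistic computed in the patients who shaped the model tends to exceed what new patients would show. The Discussion expects the biomarker to inform which areas can be observed and to help avoid surgery or radiotherapy, so calling the result validated would overstate the evidence.

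**Working it through.** **1. Aim against method.**

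| Place | What it describes |
|---|---|
| Abstract and main Background | validation |
| Statistical analysis | predictor selected by association; model created; model assessed |
| Study design | one single-arm cohort |
| Discussion | a biomarker developed in this study |

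No second data set appears. The retrospective study cited in the Background supplies a candidate, but the Statistical analysis section names no habitat, measure or scan.

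**2. The plan's own figure.** The Sample size calculation section gives 34 + 68 = 102 cases for AUC 0.70 against 0.85. With the Hanley-McNeil variance, V(A) = [A(1−A) + (n1−1)(Q1−A²) + (n0−1)(Q2−A²)]/(n1·n0), Q1 = A/(2−A), Q2 = 2A²/(1+A), n1 = 34, n0 = 68:
- A = 0.70: V = 7.603/2312 = 0.00329, SE = 0.0573
- A = 0.85: V = 4.601/2312 = 0.00199, SE = 0.0446
- 1.960 × 0.0573 + 0.842 × 0.0446 = 0.150, the required difference.

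So 102 reproduces (two-sided 0.05, power 80%). It sizes one AUC test for radiation necrosis and makes no allowance for selecting a recurrence predictor.

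**3. Chance of a false positive.** The protocol defines three structural and three physiologic habitats, hence 6 candidates at least. Twelve assumes a baseline value and one change for each. Assume independence and p<0.05 as 'strong'. With no true effect, P(at least one passes) = 1 − 0.95^k:
- k = 4: 18.5%
- k = 6: 26.5%
- k = 8: 33.7%
- k = 12: 46.0%

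Habitats from one clustering are correlated, so the true figures would be somewhat lower.

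**4. Optimism of the C-statistic.** Simulated Cox models, assessed in the same patients. The settings are assumptions: 102 patients (the protocol's evaluable cases) to 119 (132 × 0.9 = 118.8), and about 35 to 68 events. The upper end is the 68 recurrences in the sample size section; the lower is about half of that.

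*Pure-noise habitats, no clinical covariates:*

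| Model | 6 candidates | 12 candidates | New patients |
|---|---|---|---|
| All candidates entered | 0.58–0.62 | 0.61–0.67 | 0.50 |

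After univariate selection at p<0.05, C is about 0.58–0.64, but only in runs where something is selected. With 119 patients and about 62 events, counting runs with no selection as 0.50:
- 6 candidates: 0.26 × 0.587 + 0.74 × 0.50 = 0.52
- 12 candidates: 0.46 × 0.596 + 0.54 × 0.50 = 0.54

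*Selection plus four clinical covariates, 102 patients, 4 to 12 candidates:*

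| Events | True habitat effect | Same-patient C minus new-patient C |
|---|---|---|
| about 68 | none | 0.09–0.10 |
| about 68 | one, HR 1.5 per SD | about 0.05 |
| about 35 | none | 0.12–0.14 |
| about 35 | one, HR 1.5 per SD | 0.09–0.11 |

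Part of the optimism in this second table comes from fitting the clinical covariates, not from choosing among habitats. The figures show the order of magnitude; details of the set-up move them by a hundredth or two.

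**The case against.** **Validation is not the formal objective.** The primary objective and the Discussion speak of evaluating the biomarker, and Study design of investigating the value of MRI. This is true, and it is why relabelling is an acceptable remedy. The abstract and Background still promise validation, and a reader will take the result as such.

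**The earlier hypothesis is tested.** A reader might infer that the plan drops it. It does not: the hypovascular cellular habitat is among the habitats related to time to recurrence. The number of clusters and the habitat definitions are also fixed beforehand. What is missing is any status for that habitat as the one confirmatory predictor.

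**Resampling may sit in an unseen SAP.** This stands. A reader might infer that the protocol plans uncorrected performance measures; it does not say so, and such detail is commonly left to the SAP. The optimism is therefore conditional. But resampling would repair only the performance estimate. It would not turn a predictor chosen in this cohort into a validated one, and the selection rule is written into the protocol itself.

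**The magnitudes rest on assumptions.** Also true: the protocol fixes neither the candidates to be screened, nor the meaning of 'strong', nor the expected number of events. It says that habitats are computed at every scan, not that every scan is screened.

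**Conclusion.** The mismatch is established from the text alone and needs no calculation: the stated aim is validation, while the stated method is selection, model building and assessment in one cohort. Followed as written, the plan would deliver a developed biomarker.

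The size is less certain. Under independence and p<0.05, a false positive somewhere has a chance of about 26% (6 candidates) to 46% (12), less with correlation. If no correction is made, the C-statistic would be too high by roughly 0.05 to 0.14 in the assumed settings with clinical covariates.

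It is tempting to say that a noise biomarker would simply show a C near 0.59. That is not supported: after selection the figure applies only to the runs in which a candidate passes, about a quarter of them with 6 candidates. Over all runs without clinical covariates the mean is about 0.52.

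The point should be put right before analysis. It does not call the data collection into question.

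**What to change.** Choose one of two routes before the analysis starts.

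**(a) Keep the validation aim.** Name one confirmatory predictor from the earlier work: the change in the hypovascular cellular habitat, with its metric and scan interval. Test it alone at 0.05 in the primary Cox model and label all other habitats exploratory. A change exists only once a follow-up scan has been done, so enter it as a time-dependent covariate or start follow-up at a landmark at that scan. Treating it as known from the date of SRS would introduce immortal-time bias.

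**(b) Restate the aim.** Describe the study in the abstract and Background as biomarker development, and leave validation to a later cohort.

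Under either route, report the model's C-statistic, time-dependent AUC and calibration after bootstrap optimism correction, with the whole selection step repeated in each resample.

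The cost is wording, computing time and a lower reported C-statistic, by roughly 0.05 to 0.14 under the settings assumed above. No extra patients or scans are needed. A landmark under (a) also leaves out patients who recur or are lost before that scan, so some events drop from the primary test.
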